## Methods/design

### Aim of the study

The primary aim of the study is to prove that in routine clinical practice, treating patients without a tamponade dressing after hemorrhoidectomy results in a lower pain burden, and is non-inferior to the use of tamponade in terms of the incidence of severe postoperative bleeding requiring surgical revision. 

Secondary aims are to assess all patients in the group without primary tamponade dressing after surgery who needed emergency tamponade, and to compare differences between the study groups in preoperative and postoperative hemoglobin values and the use of pain medications. Quality of life and patient satisfaction will also be compared between the two treatment groups.

The safety analysis aims to compare the number of adverse events (AE) and serious adverse events (SAE) in the two study groups in order to make a statement on the potential risk to patients without a tamponade dressing after hemorrhoidectomy.

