### Design

The NoTamp study is designed as a German national, multicenter, randomized controlled clinical non-inferiority trial. Participants are randomly allocated in a 1:1 ratio to each treatment group. Randomization will be stratified per study site. Allocation to treatment groups will be performed using a centralized web-based tool. Randomization is recommended to be performed at the earliest 12 h before the start of surgery. The patient will not be informed about the result of randomization before surgery. The duration of the clinical trial for each randomized patient is 7 days. There will be no blinding of participants, physicians, nurses or outcome assessors. No interim analysis is planned.

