### Previous and concomitant medication and therapy

The NoTamp study focuses on the evaluation of post-surgical wound treatment. The surgical procedure takes place followed by postoperative care. The surgical procedures allowed in this study include Milligan Morgan’s open hemorrhoidectomy and Park’s submucosal hemorrhoidectomy. Both surgical procedures remove the excessive hemorrhoidal tissue and result in an open wound that needs further treatment.

Thrombosis prophylaxis with low-molecular-weight heparin is mandatory for all patients. Rectal cleansing (preoperative), urinary catheters, analgesics, stool control, and topical applications (ointments) are optional. Discharge management and postoperative controls are usually customized to the individual patient. Pain therapy and prophylaxis include local anesthetics, opioids, non-steroidal anti-inflammatory drugs, muscle relaxants, and other medications such as diosmin and/or sucralfate. During the postoperative period in the recovery room, the patient may receive intravenous or oral pain medication as needed. Subsequently, patients in both treatment groups may receive analgesics as needed until a correspondingly low level of pain (numeric rating scale (NRS) ≤ 3) or freedom from pain is achieved.

After hospital discharge, patients are asked to record their pain medication with type, frequency and amount of intake and to provide this information for documentation in the CRF at the study visit after 7 days. An appropriate supporting documentation template will be provided for the patient.

All previous and concomitant medication will be administered as per clinical routine and according to the patient’s needs and demands. All drugs and other treatments administered will be recorded in the CRF. Since this study represents an evaluation of clinical routine, no treatment guidelines are given.

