### Primary and secondary outcomes

Primary outcomes of the NoTamp study are maximum postoperative pain, as measured by a numerical rating scale (NRS) at four time points within 48 h after the surgical procedure, and the occurrence of postoperative bleeding with the need for surgical revision within 7 days after hemorrhoidectomy. Postoperative pain is measured at rest within routine care at 6, 12, 24, and 48 h after the surgical procedure. The most severe pain within 48 h of the surgical procedure will be compared between the treatment groups.

As a secondary outcome, the postoperative pain at each predetermined evaluation time point (6, 12, 24, and 48 h and 7 days after surgery) will be compared between treatment groups. Additionally, the change in pain intensity from 6 h after the surgical procedure to 12, 24, and 48 h and day 7 after the procedure and the development of pain between 24 and 48 h will be compared between the intervention and control group. The number of patients in the group without primary tamponade who require tamponade dressings will also be documented.

Further secondary endpoints that will be compared between the treatment groups are the use of analgesics; the lowest hemoglobin documented in clinical routine within 7 days; quality of life using EuroQuol 5 dimensions (EQ. 5D) at screening, on discharge and on day 7 and patient satisfaction on day 7. Patient satisfaction will be measured using the key figures “subjective treatment errors”; “subjective treatment success”; the satisfaction index and the expectation fulfillment scale of the Cologne Patient Satisfaction Questionnaire of Pfaff et al. [26].

For safety analysis all expected and unexpected AEs and SAEs occurring in temporal relation to the clinical trial will be documented and compared between the treatment groups. Documentation includes the causal relationship with the therapy to be investigated and/or with the previous surgical treatment. The nature of the event and the onset, end, and severity (mild, moderate, severe) of each AE will be documented. A full overview of the visit plan and the schedule of enrollment, interventions, and assessments are provided in Figs. 2 and 3.

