Pain values at all predetermined survey times and the development of pain between selected time points will be compared in the two treatment groups using the U test. The lowest hemoglobin values in the postoperative period up to day 7 will be compared in the two treatment groups using the two-sided *t* test. The amount and type of postoperative pain medication will be described by percent values for each treatment group. For the safety analysis the incidence of AEs and SAEs by category (severity) will be compared in the two treatment groups using Fisher’s exact test.

There will be no a priori planned subgroup analysis, but a multivariate analysis of all study patients (ITT population) will be performed investigating the occurrence of severe postoperative bleeding (dependent variable). In this logistic regression, the following variables are considered as possible predictors (independent variables): age, gender, surgical method used (Milligan-Morgan or Parks), severity of hemorrhoids (grade III/IV), use of tamponade (yes/no), type of tamponade used, type of anesthesia used, occurrence of intraoperative complications, preoperative hemoglobin levels, type and amount of pain therapy (in particular the performance of a pudendal block), and type and amount of anticoagulation therapy. If this multivariate analysis shows that there is a significant predictor of bleeding that is not evenly distributed within the two study groups (significance in demonstrating the comparability of the two groups), a subgroup analysis of this variable will be performed. In this case, primary and secondary endpoints will be analyzed as described previously, in the subgroups of the unequally distributed variable.

Mental illness in the study participants, preoperative pain levels, the use and type of concomitant pain therapy, and the type of tamponade used represent factors possibly influencing pain, quality of life, and patient satisfaction. The influence of these factors on the aforementioned outcomes will be examined.

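### Analgesic use is declared a between-group comparison but is only described by percentages per group, which makes the maximum-pain result harder to interpret

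*Protocol article*

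**What the plan says.** Two sections of the protocol article promise a comparison. Aim of the study sets as a secondary aim "to compare differences between the study groups in preoperative and postoperative hemoglobin values and the use of pain medications". Primary and secondary outcomes repeats it: "Further secondary endpoints that will be compared between the treatment groups are the use of analgesics".

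Statistical analysis and power calculation then fixes the method: "The amount and type of postoperative pain medication will be described by percent values for each treatment group". The sentence just before it names a *t* test for hemoglobin and reads in part: "The lowest hemoglobin values in the postoperative period up to day 7 will be compared in the two treatment groups using the two-sided". The same paragraph assigns the U test to pain at each time point and Fisher's exact test to adverse events.

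On how analgesia is given, Previous and concomitant medication and therapy says that "patients in both treatment groups may receive analgesics as needed until a correspondingly low level of pain" (NRS 3 or less) or freedom from pain is reached. It adds: "Since this study represents an evaluation of clinical routine, no treatment guidelines are given". Design states: "There will be no blinding of participants, physicians, nurses or outcome assessors".

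Two further statements bear on the point. The last paragraph of the multivariable part of the analysis section lists use and type of concomitant pain therapy among the factors that may influence pain, and says that this influence will be examined. The Discussion makes a similar commitment for all concomitant therapy.

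**The concern.** Maximum NRS within 48 h is the first primary outcome, and the bleeding hypothesis is tested only if pain is significantly lower without tamponade. The primary pain test is a U test with no term for analgesia. When analgesics are given in response to pain and towards a pain target, the recorded NRS and the drug consumed are two parts of one result.

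- If the tamponade arm receives more analgesia, the NRS contrast understates the difference in pain burden.
- If the arm without tamponade receives more, a lower NRS is not clearly a lower pain burden.

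Staff and patients know the allocation and analgesia is not standardised, so neither case can be excluded in advance. A between-arm comparison of analgesia is what would tell them apart. The plan names that comparison as an endpoint and then specifies something weaker.

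**Working it through.** **1. The sections side by side**

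| Outcome | Declared role | Stated analysis |
|---|---|---|
| Pain at each time point | compared | U test |
| Lowest hemoglobin to day 7 | compared | two-sided *t* test |
| Adverse events | compared | Fisher's exact test |
| Analgesic use | compared | percentages per group |

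The section refers detailed procedures to a statistical analysis plan, but for analgesics it is not silent: it states a method. An analysis plan that keeps to that sentence falls short of the declared aim, and one that meets the aim departs from the sentence.

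**2. How titration moves a pain difference into consumption (illustration, own assumptions)**

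Suppose analgesia removes a fraction f of the pain above NRS 3. Two patients who would both be above 3 and differ by d without analgesia then differ by (1 − f)·d on the recorded scale. With d = 0.5:

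- f = 0: 0.50
- f = 0.5: 0.25
- f = 0.8: 0.10
- f = 1: 0

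The remainder appears only as consumption.

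Effect on the test: a simulation assumed normal underlying pain with mean 5, SD 2.5 and a shift of 0.5. It used 433 per arm, scores rounded to 0–10, a two-sided U test at 5% and 500 runs. Power was 81%, 79%, 76% and 46% for f = 0, 0.5, 0.8 and 1. The Monte Carlo standard error near 80% is √(0.8 × 0.2/500) ≈ 1.8 points, so 81% and 79% are not clearly different. A rank test loses little while the ordering of patients is kept. The visible size of the difference shrinks well before the test is affected.

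The illustration uses one score instead of the maximum of four and the same f in both arms. It does not cover unequal treatment of the arms.

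**3. Whether a comparison would be informative**

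The plan's 433 per group reproduces. With bleeding rates of 4% and 8%, an 8-point margin, one-sided 5% and 80% power:

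n = (0.04 × 0.96 + 0.08 × 0.92) × (1.645 + 0.842)² / (0.08 − 0.04)² = 0.112 × 6.18 / 0.0016 ≈ 433.

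With that n per arm, at assumed levels of use:

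- 95% CI half-width for a difference in proportions, 1.96 × √(2p(1 − p)/433): 6.1 points at p = 0.30 and 6.7 points at p = 0.50.
- Power of a two-sided 5% test: 84% for 50% against 60%, and 87% for 30% against 40%.
- Smallest standardised dose difference for a U test at 80% power, taking doses as roughly normal (relative efficiency 3/π): (1.96 + 0.842) × √(2/(433 × 3/π)) ≈ 0.195 SD.

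These figures show feasibility. They do not measure harm from the present wording.

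**The case against.** The strongest reply is that percentages shown for each group already are a comparison, though a descriptive one, and that neither of the two earlier sections promises a test for analgesics. The article can say when it means a p-value, as it does for baseline data. That is fair, and a p-value is not essential. But every other outcome in the paragraph gets a named comparison, and analgesic use gets no estimate of a difference or its uncertainty.

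Second, the plan commits to examining the influence of pain therapy on pain. A reader might infer that the pain result cannot be read against analgesia at all; these commitments and the group percentages rule that out. They are a partial remedy only. No method is given. The question is whether analgesia affects pain, not whether the arms differ in analgesia. As-needed analgesia also arises after randomisation and may be affected by the allocated treatment, so adjusting for it would not give a clean treatment effect.

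Third, a reader might infer that a percentage can never express an amount, or that nearly everyone takes an analgesic so the percentages must come out equal. Neither is supported. Amounts can be shown as percentages in dose categories, and the sentence covers type as well as amount. The documents give no figure for the share of patients using analgesics.

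Fourth, the likelier direction is conservative. The pilot found more pain with tamponade, so heavier analgesia in that arm would cost power and not create a false advantage. This stands as a limit on the size of the problem. It does not remove the opposite case in an unblinded trial.

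**Conclusion.** The mismatch is real: a declared between-group comparison is given a description by percentages, and this is a stated rule, not a detail left open. The consequence is that the maximum-NRS result is hard to interpret without a between-arm comparison of analgesia. The documents do not show that it is uninterpretable or that the primary test is invalid.

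The size of any distortion cannot be derived from the documents, which give no consumption data. Under the assumptions shown, the loss of power is modest (81% to 76%) unless titration is nearly complete, while the visible pain difference among patients above NRS 3 can shrink from 0.50 to 0.10. The point should be corrected because it concerns a declared endpoint and the reading of a primary one, and because the sample is large enough for a useful estimate.

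**What to change.** Reconcile the sentence in Statistical analysis and power calculation with Aim of the study and Primary and secondary outcomes by stating a comparison by randomised arm:

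1. Proportion receiving any opioid, and each main drug class, from surgery to 48 h, with risk difference and 95% CI.
2. Where dose is recorded, cumulative opioid consumption to 48 h in a pre-stated equivalent unit, by U test with the Hodges-Lehmann difference and 95% CI.
3. Pudendal block and other local anesthesia reported separately by arm, since a cumulative dose does not capture them.

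State that the primary pain result is interpreted alongside these. Define the planned examination of pain therapy as an influence on pain, and note that it conditions on a variable arising after randomisation.

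The change affects analysis only, not patient management. All drugs given are to be recorded in the CRF. However, type, frequency and amount are spelled out only for the patient's own record after discharge, so whether inpatient dose is available for item 2 needs checking. The cost is dose conversion with pre-specified factors, whose source must be named, and a few extra secondary analyses.

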### Statistical analysis and power calculation

The analysis of the primary and secondary endpoints will be performed according to an adapted intention-to-treat (ITT) principle. There will be no interim analysis. The ITT analysis population will include all randomized participants who have undergone the surgical procedure (hemorrhoidectomy). The ITT analysis population will comprise participants assigned to the treatment group based on the randomization schedule, regardless of the treatment actually received. Randomization will be performed up to 12 h prior to the surgical intervention. However, without the surgical intervention there will be no postoperative wound that requires further treatment and thus there will be no data collected and analysis will not be possible. The study participant will therefore be excluded from the clinical trial if the scheduled surgery is not performed. Patients who are excluded from the trial after randomization and before the start of the observation period (postoperative wound care with or without tamponade) are replaced by another study participant in order to achieve the required number of cases. The randomization sequence will be continued. The next patient does not receive the randomized allocation of the excluded patient. The study will be continued until the required number of evaluable patients has been reached. Due to complications it may not be possible to comply with the randomly assigned treatment regimen in a very small number of patients. These patients will not be excluded from the study. Study participants will also be excluded from the clinical trial if a surgical procedure other than Milligan-Morgan or Parks is performed, which does not result in an open wound.

Details of participants’ baseline characteristics including preoperative pain and hemoglobin levels will be provided, but the data will not be compared statistically (by calculating the *p* value) because any differences between groups at this point must arise by chance (if randomized properly).

As a secondary approach, a per-protocol (PP) analysis will be performed excluding patients with any serious protocol deviations, if applicable. The safety analysis will be performed based on the as-treated (AS) population.

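### The significance-triggered subgroup rule conflicts with the refusal to test baseline balance, and its candidate list includes the treatment and variables that treatment can affect

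*Protocol article*

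**What the plan says.** All statements are in the Protocol article, section Statistical analysis and power calculation.

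- **Baseline.** Characteristics, with preoperative pain and hemoglobin among them, are described but not tested. The stated reason is this: "because any differences between groups at this point must arise by chance (if randomized properly".
- **Subgroups.** "There will be no a priori planned subgroup analysis, but a multivariate analysis of all study patients (ITT population) will be performed". That analysis is a logistic regression with severe bleeding after surgery as its outcome.
- **Candidate predictors.** There are eleven. Seven are age, gender, surgical method, hemorrhoid grade, anesthesia type, complications during surgery, and anticoagulation. Two concern the treatment: "use of tamponade (yes/no), type of tamponade used". The other two are worded as follows: "preoperative hemoglobin levels, type and amount of pain therapy (in particular the performance of a pudendal block".
- **Trigger.** The rule applies under this condition: "If this multivariate analysis shows that there is a significant predictor of bleeding that is not evenly distributed within the two study groups". How unevenness is judged stands in a parenthesis just before the order to act on it: "significance in demonstrating the comparability of the two groups), a subgroup analysis of this variable will be performed".
- **Consequence.** The scope of the re-analysis is wide: "primary and secondary endpoints will be analyzed as described previously, in the subgroups of the unequally distributed variable".

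**The concern.** Four things are fixed badly in this text.

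1. Significance of a between-group difference is rejected as uninformative in one paragraph and used as a decision criterion in another. A plan with no prespecified subgroups thereby acquires data-driven ones covering the primary endpoints.
2. The treatment is on the list that feeds the trigger. Tamponade use differs between the arms by design, so the unevenness condition is always met for it, and no exemption is written.
3. Some candidates are poorly defined or can follow from treatment. The text does not say whether tamponade use means the randomised arm or a tamponade actually received. If it means received, a tamponade placed because of bleeding would enter as a predictor of bleeding. Tamponade type is defined only where a tamponade was used. Postoperative analgesics are given as needed, and pain is the outcome the treatment is expected to change.
4. The model has few events for its size.

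At stake are unstable odds ratios for the trial's key safety event, and subgroup non-inferiority statements that the trial was not sized to make.

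**Working it through.** **Inputs from the article.** Bleeding 4% (control) and 8% (no tamponade), margin 8 percentage points, power 80%, 433 per group, 866 in total. The test is one-sided at 5% (90% confidence interval).

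**Reproducing the plan's figure.** n per arm = (1.645 + 0.842)² × (0.04×0.96 + 0.08×0.92) / (0.08 − 0.04)² = 6.18 × 0.112 / 0.0016 ≈ 433. This matches, and 866 × 1.10 ≈ 953. The inputs below are therefore the plan's own.

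**The conflict.** Age, gender, grade and preoperative hemoglobin are baseline items covered by both statements; preoperative hemoglobin is named in both. Variables settled after randomisation are not covered by the baseline sentence, so the contradiction is confined to these four.

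**Events per variable.** Expected events = 433 × (0.04 + 0.08) = 52.
- 11 variables, one term each: 52/11 = 4.7.
- 13 parameters (minimum coding, with separate terms for type and amount of pain therapy and of anticoagulation): 52/13 = 4.0.
- 20 parameters (assumed, for multi-category coding): 52/20 = 2.6.
- Both arms at 4%: 433 × 0.08 = 34.6 events, or 2.7 per parameter at 13.

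**The trigger on tamponade use.** At 4% versus 8% with 433 per arm, the unadjusted two-sided 5% comparison is significant with probability 0.70 (normal approximation) or 0.707 (exact calculation). In 600 simulated trials with tamponade and 12 unrelated covariates in the model, tamponade was significant in 71%. One run did not converge. If use means allocation, each resulting subgroup is exactly one arm. If it means received, each subgroup is one arm plus non-randomised crossovers.

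**Tamponade use plus type.** With an intercept, a use indicator and an indicator for each of two types, use equals the sum of the type indicators. The design matrix has rank 3 with 4 columns, so full coding cannot be fitted.

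**The trigger on noise covariates.** Both conditions must fall on the same variable. With 12 independent null covariates:
- At least one significant in the bleeding model: 1 − 0.95¹² = 46% (simulated 46%).
- Both conditions on the same one: 1 − (1 − 0.05²)¹² = 3.0% (simulated 2.8%).
- For the four baseline items, the imbalance condition alone: 1 − 0.95⁴ = 18.5%.

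**Power in a subgroup.** Power = Φ(0.04 / √(0.112/m) − 1.645), with m patients per arm and the 8-point margin of the sample size section.
- m = 433: 80%.
- m = 216.5 (half): 54.5%, with about 8.7 expected control events.
- m = 108 (quarter): 34%, with about 4.3 expected control events.

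**The case against.** The parenthesis about comparability suggests that covariates were meant, and an analyst would hardly split the trial by its own treatment. That is a fair reading of intent. The rule as written still contains no exemption, so the 70% describes the literal text, not a likely analysis.

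A reader might infer that the model uses tamponade received. The documents do not establish this. The model is placed in the ITT population, which is grouped by allocation, and emergency or postoperative tamponade is treated elsewhere as a separate quantity. The supported point is that the term is ambiguous.

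A reader might also take 1 − 0.95¹⁰ = 40%, the chance of at least one significant imbalance among ten independent factors, as the false-trigger rate. It covers only half of a two-part condition. On pure noise the full rule fires in about 3% of trials.

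Anesthesia, surgical method and intraoperative complications precede placement of the tamponade, which happens after hemostasis. They can be influenced only through knowledge of an unblinded allocation made before surgery. That risk is weaker than the one for analgesic amount. For pain therapy, the text stresses the pudendal block, so the charge is limited to the postoperative amount.

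Finally, the variables are possible predictors, and coding and selection can be settled in a statistical analysis plan. This softens the events-per-variable point. It does not remove the trigger or the composition of the list, which the article states outright.

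**Conclusion.** The point holds, as a recommended change and not a threat to the main result. The baseline statement and the subgroup trigger conflict for the four baseline items and must be reconciled. The trigger's candidate list includes the treatment, a variable defined only where a tamponade was used, and a variable that treatment can affect. With about 52 events, a full model would have at most 4.7 per variable and about 4 with minimum coding.

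The practical harm lies in the treatment and post-randomisation variables and in underpowered subgroup claims, not in frequent false triggering by baseline noise.

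The figures assume the planned rates, independent covariates with arbitrary prevalences in the simulation, and equal arms within a subgroup. That the model would be unstable is a judgement; the documents set no events-per-variable threshold. The confidence-interval rule for the primary bleeding test does not depend on this model or on the subgroups.

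**What to change.** - Delete the rule that turns a significant, unevenly distributed predictor into a subgroup analysis.
- Fit the bleeding model with randomised arm, named as such, plus a short fixed list of factors known before randomisation and already collected: for example age, planned surgical method, grade, preoperative anticoagulation and preoperative hemoglobin. With one term each, this is 6 terms, or 52/6 = 8.7 events per term.
- State that this adjusted estimate, which uses all patients, is how chance imbalance will be handled.
- Remove tamponade type and postoperative analgesic amount from the model. Postoperative tamponade in the no-tamponade arm stays a descriptive outcome, as already planned.

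Penalised estimation and interaction terms are optional and can be left to the statistical analysis plan. The change costs wording only: no new data and no change to the primary test. The downside is fewer exploratory predictors of bleeding.
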